### Plans for assessment and collection of outcomes {18a}

#### Biochemical measurements for outcomes

All laboratory analyses will be performed in a central laboratory. After a 12-h overnight fast, blood samples are collected at baseline and at 12 weeks to evaluate the biomarkers of glucose and lipid metabolism, including blood glucose concentrations measured 0 to 120 min after meal, HbA1c, fasting C peptide, fasting insulin, liver enzymes, inflammatory factor, and blood lipid.

#### Physical examination

Body weight, height, waist circumference, and hip circumference will be measured at baseline and 12 weeks later. The body composition is analyzed by InBody270, available at the hospital’s endocrinology department. BMI is calculated according to the formula. Systolic and diastolic blood pressure will be tested by a sphygmomanometer at every visit.

#### Hepatic steatosis

Transient elastography (FibroScan) would be performed after 8-h overnight fasting to assess hepatic steatosis and fibrosis according to liver stiffness measurements (LSM) and controlled attenuation parameter (CAP) score. The severity of fatty liver will be evaluated at baseline and 12 weeks later.

#### Dietary assessments

Three days of 24-h dietary questionnaire would be completed at the beginning and at the end of the study; data were collected by a professional nutritionist.

### Plans to promote participant retention and complete follow-up {18b}

To promote participant retention and complete follow-up, we will educate patients on the importance of follow-up visits of the therapy. And we make it available to all subjects to contact the principal researcher at any time and are responsible for all inspection fees and expenses for medicine.

### Data management and analysis {19}

Patient data will be recorded in case report form and then copied into Excel spreadsheets. To ensure the quality of data, we will provide training regarding data management and study-related procedures prior to the commencement of the trial to all researchers of this study.

### Confidentiality {27}

The trial and participant data will be kept confidential and stored in a secure place in Shunde Hospital, Southern Medical University (The First People’s Hospital of Shunde). All data will be entered into a computer software, using standard coding to ensure the confidentiality of the participants.

### Plans for collection, laboratory evaluation and storage of biological specimens for genetic or molecular analysis in this trial/future use {33}

Blood and stool samples are stored by the sponsor in a biobank for further research to enhance the prevention and management of diseases.

## Statistical methods

### Statistical methods for primary and secondary outcomes {20a}

All collected variables will be statistically analyzed by SPSS 28.0 statistical software and GraphPad Prism 8. Continuous variables will be assessed by analysis of covariance (ANCOVA). Categorical data will be assessed by the *χ*^2^ test. Differences between values within each arm will be evaluated using paired Student’s *t*‐tests. Nonparametric tests will be used to evaluate differences in non-normally distributed variables. Correlation analysis and multiple linear regression analysis will be used to analyze the synergistic effects of lifestyle modification and metformin. *P* < 0.05 will be used as the significance level.

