### Methods/design {8}

The study is a randomized, single-center, parallel group, superiority clinical trial. All patients who meet eligibility criteria are invited to this study and then assigned to different groups with a 1:1:1 allocation rate, receiving 12 weeks of follow-up.

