### Methods in analysis to handle protocol nonadherence and any statistical methods to handle missing data {20c}

Data analysis will be performed according to the intention-to-treat principles. Per-protocol analyses will be done only for patients completing 12 weeks of therapy. Multiple imputation will be employed under the assumption of “missing at random.”

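### The nonparametric fallback for skewed outcomes probably gives up the baseline value, and the within-arm paired t-tests are not marked as descriptive

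*Protocol article*

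**What the plan says.** All rules on this point stand in the protocol article, statistical methods {20a}. ANCOVA is the method for continuous variables; its covariate is not named. For outcomes that are not normally distributed the rule is: "Nonparametric tests will be used to evaluate differences in non-normally distributed variables". No test is named. For change within an arm: "Differences between values within each arm will be evaluated using paired Student’s" t-tests. A single threshold of P < 0.05 covers everything in the section. Synergy has its own sentence: "Correlation analysis and multiple linear regression analysis will be used to analyze the synergistic effects of lifestyle modification and metformin".

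Three other sections matter. Methods/design {8} reads: "The study is a randomized, single-center, parallel group, superiority clinical trial", with three arms allocated 1:1:1. Outcomes {12} lists HOMA-IR and triglycerides as secondary outcomes, and the section on biochemical measurements has blood taken at baseline and at 12 weeks. On missing data, {20c} states: "Multiple imputation will be employed under the assumption of" missing at random.

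**The concern.** Two rules in {20a} sit beside the between-arm ANCOVA and can lead away from it.

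- **The fallback.** An outcome judged non-normal leaves ANCOVA for a nonparametric test. In SPSS or GraphPad Prism the usual choices are Mann-Whitney or Kruskal-Wallis, and neither accepts a covariate. HOMA-IR and triglycerides are plausibly right-skewed (an assumption; the article does not say so). For them the baseline value would be collected and then not used, or used only through a change score. A bare rank-test P value also supplies no estimate and standard error to pool across imputed data sets.
- **The within-arm tests.** Change from baseline includes regression to the mean and the effect of taking part in a trial, and it does not compare arms. Every arm receives an active intervention, so all three may improve. One arm significant and another not is then a likely pattern even when the arms do not differ, and it is easily misread as a treatment difference.

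**Working it through.** The plan gives no figure on this point to reproduce. Its 31 per group is taken as given. That 0.4 and 1.5 lead to 221 per arm in a two-sided two-sample calculation is a separate matter on which nothing here depends.

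**Part 1: power of the fallback**

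Inputs from Sample size {14}: 31 per arm, 20% attrition, so 31 × 0.8 = 24.8, about 25 completers; two-sided 5% assumed. Inputs assumed because the article gives none: log-normal outcome, shift of 0.6 SD on the log scale, baseline correlation r of 0.5 to 0.7, and log SD of 1.0 for strong skew. Two arms are compared.

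Hand check, with z = 0.6 / √(2(1 − r²)/31) and power ≈ Φ(z − 1.96):

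- Log-scale ANCOVA, r = 0.5: 0.6/√(1.5/31) = 2.73, power about 78%.
- Log-scale ANCOVA, r = 0.6: 0.6/√(1.28/31) = 2.95, power about 84%.
- Log-scale ANCOVA, r = 0.7: 0.6/√(1.02/31) = 3.31, power about 91%.
- Rank test on 12-week values, whatever r: 0.6/√(2/31) = 2.36, times √(3/π) for rank efficiency = 2.31, power about 64%.

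Simulation, log SD 1.0, 3,000 runs per setting (standard error about √(0.6 × 0.4/3000) = 0.9 points):

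| Method, 31 per arm | r = 0.5 | r = 0.6 | r = 0.7 |
|---|---|---|---|
| Rank test, 12-week values | 60% | 61% | 61% |
| Rank test, change (treatment lowers the outcome) | 44% | 53% | 64% |
| ANCOVA, untransformed | 54% | 59% | 68% |
| ANCOVA, log scale | 75% | 82% | 88% |

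Other runs put log-scale ANCOVA at 76%, 82% and 90%. Rank ANCOVA (ranks of outcome adjusted for ranks of baseline) lies between 73% and 88% over the same correlations. The gap between the first and last rows is 15, 21 and 27 points. At 25 completers and r = 0.6 the rank test has 53% and log-scale ANCOVA 75%.

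The change-score row depends on direction. If the treatment raises a log-normal outcome, the same test has 61 to 81%. A beneficial treatment lowers HOMA-IR and triglycerides, so the row shown is the relevant one: under strong skew the change score falls below the follow-up rank test at r = 0.5 and 0.6, and slightly exceeds it at r = 0.7.

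With 25 per arm, a 0.7 SD shift and strong skew, the rank test on 12-week values has 64% and log-scale ANCOVA 71% at r = 0.3. At r = 0.7 they have 65% and 92%. The loss is therefore about 7 to 27 points over that wider range.

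**Part 2: within-arm tests**

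Inputs: change 0.4 and SD 1.5 (Sample size {14}), read here as a within-arm change and its SD; 25 completers per arm; the same true change in all three arms.

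- Standardised change 0.4/1.5 = 0.267. Paired t-test power with n = 25 is p = 0.249.
- Not all three arms agree: 1 − p³ − (1 − p)³ = 1 − 0.015 − 0.424 = 0.561.
- Exactly one of two given arms significant: 2 × 0.249 × 0.751 = 0.374.
- Co-intervention significant and at least one other arm not: 0.249 × (1 − 0.249²) = 0.234. With n = 31, p = 0.301 and this is 0.301 × (1 − 0.301²) = 0.274.

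The 56% varies with the assumed change: 75% at 0.4 SD and 54% at 0.56 SD, both with 25 per arm.

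**The case against.** Much of the other side stands.

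- **Loss of baseline is inferred.** A reader might conclude that the plan deliberately drops baseline adjustment. The text names neither the ANCOVA covariate nor the nonparametric test. A rank test on change would use baseline in part, and rank ANCOVA would adjust for it. The named test and the criterion for non-normality are commonly left to a statistical analysis plan, so their absence here is not a fault.
- **Efficacy is not based on paired tests.** A reader might infer that it is. No section says so: ANCOVA is the general method for continuous outcomes, and the trial is described as a parallel-group superiority trial. Reporting within-arm change beside it is common.
- **The power loss depends on the comparator.** Log-scale ANCOVA appears nowhere in the protocol. Against untransformed ANCOVA, ranks do as well or slightly better under strong skew at r = 0.5 and 0.6 (60% against 54%, 61% against 59%). So it is not true in general that the fallback makes the plan less powerful.
- **Scope.** The outcomes most likely to be affected are secondary. Nothing shows that HbA1c or the measure of NAFLD severity would be skewed.
- **Imputation.** Rank-based location-shift estimates exist, and {20c} does not say which analyses use imputation. This is a minor inconvenience.

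What remains is that the article does state a switch of method by distribution, whose usual form is unadjusted, and does plan within-arm significance tests under the same threshold as everything else. Better methods need no new data.

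**Conclusion.** The point holds as an inexpensive improvement to the analysis wording. It is not a defect that undermines the trial. On the likely reading of the fallback, skewed secondary outcomes would be tested with about 60% power where log-scale ANCOVA would give about 75 to 90% and rank ANCOVA 73 to 88%. These figures assume a log-normal outcome, 31 per arm, a 0.6 SD shift and a correlation of 0.5 to 0.7; the article gives neither the shift nor the correlation. A rank test on change recovers part of the loss only when the correlation is high or the skew and direction are favourable. Untransformed ANCOVA is not a reliable alternative under strong skew.

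The within-arm tests are a risk of misreading. Identical arms would give discordant significance about 56% of the time with 0.4, 1.5 and 25 completers. That size assumes that 0.4 and 1.5 describe change within an arm, and it harms inference only if someone draws efficacy conclusions from these tests, which the protocol does not propose.

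**What to change.** In {20a}:

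1. Analyse each continuous outcome by ANCOVA on the 12-week value, with its own baseline as covariate.
2. For skewed outcomes, naming HOMA-IR and triglycerides in advance, use ANCOVA on log values with log baseline as covariate, reported as ratios of geometric means with 95% CI. Rank ANCOVA is an acceptable alternative, but it gives no directly interpretable effect and pools less easily across imputations. Keep unadjusted rank tests as sensitivity analyses only.
3. Report within-arm change as mean and 95% CI, labelled descriptive, and state that efficacy conclusions rest on between-arm contrasts.

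The cost is a few sentences, since baseline and 12-week values are already collected. The one downside is that log-scale results are read as ratios and not as differences in original units.

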**Methods:**

Participants will be recruited in this single-center, randomized clinical trial through telephone interview. All participants will be assigned randomly at a 1:1:1 ratio to three groups and treated with lifestyle modification including calorie-restricted dietary and exercise therapy, 500–2000 mg/day metformin, or treated with both lifestyle modification and 500–2000 mg/day metformin (the co-intervention group) for 12 weeks. The primary outcomes are changes in glycemic control and severity of fatty liver from baseline to 12 weeks of follow-up.

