**Discussion:**

This trial is designed to clarify whether lifestyle intervention combined with metformin has synergistic effects on glycemic control, attenuating the progression of NAFLD in NAFLD patients with newly diagnosed T2DM.

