### Objectives {7}

The primary objective of this randomized clinical trial is to evaluate the efficacy of lifestyle modification combined with metformin in NAFLD patients with newly diagnosed type 2 diabetes.

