## Interventions

### Explanation for the choice of comparators {6b}

A lifestyle modification plays a fundamental role in the management of patients with newly diagnosed T2DM or NAFLD. However, many diabetic patients or NAFLD patients fail to achieve clinical goals in clinical practice. Metformin is the most common anti-hyperglycemic agent. The protective effect in chronic liver disease is controversial. We want to further clarify whether there is a synergistic reaction between lifestyle modification and metformin in NAFLD patients with newly diagnosed type 2 diabetes.

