Metformin is the most common anti-hyperglycemic agent. Many studies have reported benefits of metformin in obesity, cardiovascular disease (CVD), and liver disease. Metformin treatment prevents obesity induced by a high-fat diet [21]. In humans, metformin decreased the incidence of CVD [22]. It has been shown that metformin reduced hepatocellular carcinoma incidence and improved survival [23]. Metformin caused a reduction of liver triglyceride content in ob/ob mice [24]. The benefits of metformin in treating NAFLD were also observed in human research [25]. But there is still controversy [26]. A randomized-controlled study of metformin monotherapy was rarely conducted in the NAFLD population with diabetes. Evidence related to the effectiveness of metformin in NAFLD patients with newly diagnosed T2DM is still insufficient.

Studies indicated that lifestyle modification (diet and physical activity interventions) regulated AMP-activated protein kinase (AMPK), a key molecular player linked with the function of energy metabolism [27]. It has been reported that metformin could regulate hepatic glucose output and lipid metabolism through the AMPK-dependent pathway [28]. In addition, recent evidence has shown that metformin may exert its antidiabetic effects by affecting the composition and function of the gut microbiota [29]. Diet and physical activity interventions have shown a potential role in modulating gut microbial balance [30]. As mentioned above, lifestyle modification and metformin may share the same biological target in the management of metabolic diseases. It has not been reported whether the superposition of these two interventions can be synergistic. Thus, we set up a group providing both lifestyle modification and metformin in our study.

There are several limitations in our study. First, the adherence for longtime lifestyle intervention may not be high. To minimize bias, we make regular return visits and strengthen education. Second, the self-reported dietary intake is subject to bias and limitations. Third, some subjects may be intolerant to metformin.

In summary, this study will assess the synergistic effect of intensive lifestyle combined with metformin on glycemic control, hepatic steatosis, and fibrosis.

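### The plan promises a test of synergy, but three arms without a neither-treatment group cannot estimate it

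*Protocol article*

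**What the plan says.** Three places in the protocol article present synergy as something the trial will answer. The Discussion part of the Abstract says the trial is meant to "clarify whether lifestyle intervention combined with metformin has synergistic effects on glycemic control". The section on the choice of comparators {6b} asks "whether there is a synergistic reaction between lifestyle modification and metformin". The closing Discussion states that "this study will assess the synergistic effect of intensive lifestyle combined with metformin on glycemic control, hepatic steatosis, and fibrosis", and the same section gives the open question of synergy as the reason for having a combined group.

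The statistical methods section {20a} then assigns an analysis to it: "Correlation analysis and multiple linear regression analysis will be used to analyze the synergistic effects of lifestyle modification and metformin".

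On the design, the Abstract says "All participants will be assigned randomly at a 1:1:1 ratio to three groups". The Intervention section {11a} and the allocation section {16a–c} name the groups as lifestyle modification, metformin and co-intervention, with 31 participants each. No placebo, usual-care or untreated group is described, and no assumption is stated about how participants would change without treatment.

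The formal objective {7} is worded differently. It is to "evaluate the efficacy of lifestyle modification combined with metformin in NAFLD patients with newly diagnosed type 2 diabetes", with no mention of synergy.

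**The concern.** Synergy is a statement about departure from additivity. To judge it, one must know what each treatment does compared with no treatment, and then whether the pair does more than the two effects added together. The reference for that is the neither-treatment group, which this trial does not have.

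What the three arms can show is that the combination beats a single treatment. That is a different and weaker statement. It is also true when the effects simply add up, and it can be true when each treatment partly cancels the other. If the plan is followed as written, a favourable result for the combination could be published as synergy although the data are equally compatible with additivity or antagonism. The conclusion announced in the Abstract and repeated in the closing Discussion would then have no support.

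**Working it through.** The plan gives no figure for synergy to reproduce. The check asks whether the quantity can be estimated at all, and that depends only on which arms exist.

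**1. Coding the arms** (Intervention {11a}; allocation {16a–c}). Let L = 1 if lifestyle modification is given and M = 1 if metformin is given.

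| Arm | Mean change | Intercept | L | M | L×M |
|---|---|---|---|---|---|
| Lifestyle | A | 1 | 1 | 0 | 0 |
| Metformin | B | 1 | 0 | 1 | 0 |
| Both | C | 1 | 1 | 1 | 1 |
| Neither (not in the trial) | D | 1 | 0 | 0 | 0 |

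**2. The target.** Interaction = (C − D) − (A − D) − (B − D) = C − A − B + D.

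**3. Rank.** With 31 participants in each of the three actual arms, the design matrix has four columns and rank 3. Its null vector is (1, −1, −1, 1): adding any constant to the intercept and the interaction, and subtracting it from both main effects, leaves every fitted mean unchanged. Adding a baseline covariate gives rank 4 for five columns, so the deficiency remains. With a fourth, neither-treatment arm the matrix has full rank (4 of 4, or 5 of 5 with the covariate). Sample size, SD and alpha play no part.

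**4. What a regression would return.** One term has to be dropped, and the choice settles what the remaining coefficients mean:

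- Drop L×M: the L coefficient is C − B, the M coefficient is C − A, and the intercept is A + B − C. Additivity is imposed, not tested.
- Drop L: the coefficient labelled L×M is C − B (both versus metformin).
- Drop M: the coefficient labelled L×M is C − A (both versus lifestyle).
- Drop the intercept: the coefficient labelled L×M is C − A − B, which silently sets D = 0.

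**5. Illustration with assumed 12-week HbA1c changes** (not from the protocol): A = −0.6, B = −0.8, C = −1.2. Negative values are improvement, so a negative interaction is synergy. The unknown D is written c.

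Interaction = −1.2 + 0.6 + 0.8 + c = 0.2 + c.

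| Untreated change c | Interaction | Reading |
|---|---|---|
| −0.3 | −0.1 | synergy |
| −0.2 | 0.0 | exactly additive |
| 0 | +0.2 | antagonism |
| +0.3 | +0.5 | antagonism |

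In every row the combination beats lifestyle by 0.6 and metformin by 0.4. From the same three means, the coefficient labelled interaction in step 4 would be −0.4 (L dropped), −0.6 (M dropped) or +0.2 (intercept dropped).

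**6. Correlation analysis.** It describes association between observed variables. It does not supply D.

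**7. Size of the task if a fourth arm existed.** Take the SD of 1.5 and difference of 0.4 from Sample size {14}, two-sided alpha 0.05 (the sidedness is my assumption) and 25 evaluable per arm after 20% attrition (31 × 0.8 = 24.8).

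- SE of the interaction = 1.5 × √(4/n): 0.54 for n = 31 and 0.60 for n = 25.
- Power for an interaction of 0.4: about 11% and 10%.
- Interaction detectable with 80% power: about 1.5 and 1.7 HbA1c points.
- An interaction of 0.4 would need about 442 evaluable per cell, or 442/0.8, about 553, with attrition.

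**8. Power of what can be estimated.** For one contrast of two arms, SE = 1.5 × √(2/n). With the same inputs, power for a difference of 0.4 is about 18% at 31 per arm and 15% at 25.

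**The case against.** The strongest reply is that synergy is not the formal objective. Objectives {7} speaks of the efficacy of the combination, the Introduction {6a} of metformin as an adjuvant to lifestyle modification, and the design section {8} of superiority. All of these can be answered from three arms, and the ANCOVA comparison in {20a} is unaffected. This stands as a limit on scope: the defect lies in the synergy analysis and wording, not in the objective of {7}. It does not rescue a sentence in {20a} that names synergy as what the regression will analyse.

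Second, {20a} does not write out a model. The four-coefficient form is the natural reading, but a regression on actual metformin dose or dietary intake is conceivable, and such detail is often left to an analysis plan. The article does not state such a model, however. Those exposures arise after randomisation, so the comparison would no longer be a randomised one, and reaching the neither-treatment state would need extrapolation. An analysis plan can specify a model, but it cannot supply a missing arm.

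Third, the design is not wholly silent. If one assumes that HbA1c does not rise without treatment (D ≤ 0), an observed C − A − B below zero would imply a more than additive reduction. This is correct, but the protocol states no such assumption. In the illustration C − A − B is +0.2, so the bound would settle nothing.

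Fourth, the word may be used loosely for added benefit. The closing Discussion links it to a shared biological target of the two treatments, which reads as an interaction hypothesis. If only added benefit is meant, the wording still needs correcting.

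**Conclusion.** The concern holds. The synergy analysis named in {20a} targets a quantity that the three randomised arms do not identify: rank 3 for four coefficients, with or without a baseline covariate. The interaction shifts one for one with the unobserved untreated change. In the illustration, a range of ±0.3 in that change carries it from −0.1 to +0.5, across zero, with identical trial data. The HbA1c means are assumed and show only this dependence; they do not estimate an error in this trial. The rank result rests on no numerical assumption.

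The metformin arm also receives health education under {11a}, so the lifestyle factor is not cleanly absent there. This blurs the contrast further but does not drive the conclusion.

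This must be fixed, because it affects the conclusion that the Abstract and the closing Discussion announce, and no amount of data from these arms can repair it.

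**What to change.** - In {20a}, delete the correlation and regression analysis of synergy. Replace it with two ANCOVA contrasts with 95% confidence intervals: co-intervention versus lifestyle modification, and co-intervention versus metformin.
- State that added benefit of the combination is claimed only if both contrasts favour it at two-sided 0.05. Because both are required, the two contrasts need no alpha adjustment within one outcome. This does not cover several outcomes, so the rule must name the outcome it applies to. The Abstract, Outcomes {12} and Sample size {14} differ on which outcome is primary, and that has to be settled separately.
- In the Abstract, {6b} and the Discussion, replace the synergy wording with superiority of the combination to either component alone.
- State plainly that synergy cannot be tested in this design.

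The cost is wording, plus the notice to the ethics committee that {25} requires for changes to objectives or design. No arm, participant or treatment changes, and the sponsor gives up only a claim that the design could not support. The change does not cure low power: at the protocol's own 0.4 and SD of 1.5, each contrast has about 15% to 18% power, and requiring both cannot raise it. A fourth arm would make synergy estimable, but the present group size would detect only an interaction of about 1.5 to 1.7 points. Whether an untreated arm is acceptable is a clinical question that is not judged here.
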